### Study Randomization

Four treatment arms are used to investigate the effective dose and safety profile of linagliptin in the study population. Randomization will be based on the Zelen rule [13] and follow a predefined allocation ratio of 2:2:2:1 (linagliptin 5 mg: linagliptin 10 mg: voglibose: placebo). Allocation to treatment groups is balanced for the potentially confounding effects of patient background and baseline characteristics, HbA_1c _(stratified into two categories; < 8.5% and ≥ 8.5%), the number of pre-study use of antidiabetic drugs, gender and study site.

Treatment allocation is conducted by a sponsor-independent contractor. Following informed consent, the investigator completes a registration form that is sent to the allocation center. The registration form includes data on the subjects' inclusion and exclusion criteria. After receiving the registration form, the allocation center sends a registration report to the investigator. The investigator confirms that the patient satisfies the study criteria and sends a second registration form to the allocation center once the 4-week washout period is completed. The allocation center randomizes the patient according to the pre-defined criteria above and this information is provided to the investigator. Randomization is done once at the enrollment of study. At the randomization after the enrollment, patients are assigned, to 6 groups: placebo - linagliptin 5 mg, placebo - linagliptin 10 mg, linagliptin 5 mg, linagliptin 10 mg, voglibose - linagliptin 5 mg, and voglibose - linagliptin 10 mg. Therefore all patients ultimately take either linagliptin 5 mg or 10 mg, unless they withdraw or drop out the study.

### Statistical analysis

The statistical analyses are performed on an intention-to-treat basis. The full analysis dataset (FAS) is described in the ICH E9 guidelines [14], and is defined as the proposed analysis dataset for efficacy. The procedures followed are described below.

#### Analysis for the primary endpoint

Baseline glycosylated hemoglobin levels and the number of antidiabetic drugs used before study enrollment are included in the model as covariates.

Changes in HbA_1c _level from baseline to 12 weeks of linagliptin treatment are analyzed in accordance with the model below, in order to compare with placebo in the double-blind treatment phase:

Where:

*y*_*ijk *_: change in HbA_1c _at 12 weeks from baseline

*BHbA1c*_*i *_: HbA_1c _of i-th patient at baseline (i = 1, 2,..., n)

*Dose*_*j *_: j-th dose group (j = 0: placebo, 1: 5 mg, 2: 10 mg)

*Diabtreat*_*k *_: number of previously used antidiabetic drugs (k = 0: no treatment, 1: one antidiabetic drug, 2: two antidiabetic drugs)

Comparisons conducted at 12 weeks are between linagliptin and placebo. Patients who received placebo for 12 weeks and are then randomized to receive either linagliptin 5 mg or 10 mg are excluded from this analysis. Values of HbA_1c _following treatment with linagliptin are to be compared with those for voglibose after 26 weeks if linagliptin treatment fails to achieve a statistically significant difference in HbA_1c _levels relative to placebo (primary comparison dose at 12 weeks). The dosing schedule for linagliptin increases from 5 mg to 10 mg during study if linagliptin 5 mg fails to demonstrate superiority to placebo at 12 weeks. In addition, the study stops if neither of the linagliptin arms shows statistically significant differences from placebo in HbA_1c _levels at 12 weeks.

The model for HbA_1c _at 26 weeks is:

Where:

*y*_*ijk *_: Change in HbA_1c _at 26 weeks from baseline

*HbA1c*_*i *_: HbA_1c _of i-th patient at baseline (i = 1, 2,..., m)

*Drug*_*j*_: j-th treatment group (j = 1:5 mg, 2:10 mg, 3:voglibose)

*Diabtreat*_*k *_: number of previously used antidiabetic drugs (k = 0:no treatment, 1:one antidiabetic drug, 2:two antidiabetic drugs)

Comparisons for HbA_1c _between groups are performed weekly by the closed testing procedure [15]. No formal analysis will be performed for safety and tolerability data collected during the three stages of the study. Data will be summarized in terms of treatment received.

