**Figure 1 F1:**
[figure not shown]
**Study Design**.

Initially, patients will undergo a washout period where they receive placebo for 4 weeks after providing informed consent. Following the washout period, eligible patients will be randomized to one of four treatment arms (placebo [A]; linagliptin 5 mg [B]; linagliptin 10 mg [C]; or voglibose 0.6 mg [D]). Patients randomized to Group A will receive a placebo for 12 weeks after which they will receive linagliptin for 40 weeks; patients in the Group B (linagliptin 5 mg) and Group C (linagliptin 10 mg) treatment arms will receive the study drug for up to 52 weeks. Patients randomized to Group D (voglibose 0.6 mg) will receive the treatment for 26 weeks after which they will be switched to linagliptin for 26 weeks (Figure 1). The treatment change to linagliptin in Groups A and D involves an additional patient randomization to either 5 mg or 10 mg, from which data on the long-term safety and tolerability of linagliptin will be collected. The doses of linagliptin used in this study are based on previous reports of DPP-4 activity in Japanese T2DM patients [11].

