The study design was selected to reduce the number of patients required to undergo a prolonged placebo exposure by employing an imbalanced randomization (placebo:linagliptin 5 mg:linagliptin 10 mg:voglibose = 1:2:2:2). Using this biased treatment allocation approach, it is possible to minimize the potentially unethical exposure of patients to placebo while maintaining sufficient power to complete the primary statistical comparison. Data after 16 weeks of placebo treatment can be useful for determining a true baseline (treatment naïvety) because any underlying glycemic controlling effects of prior antidiabetic treatment should have had sufficient time to reverse. The 16 week data for glycosylated HbA_1c _levels in the placebo group will not be included in any comparison, but instead will be viewed as an indication of the study population's baseline HbA_1c _values in the absence of the potentially confounding residual effects of previous therapies. A similar number of patients are needed to demonstrate the non-inferiority or superiority of linagliptin to placebo under imbalanced randomization and to voglibose. The study design can also be sufficiently powered for detecting statistically significant differences between linagliptin and placebo or voglibose. Using the methods described, we have calculated that this can be achieved without markedly increasing the number of subjects needed.

The efficacy of short term linagliptin treatment in Japanese T2DM patients was reported by Kanada et al [11]. We set the one-sided hypotheses (2.5% statistically significant level) in the present study as the efficacy of linagliptin is expected to show significant superiority to placebo or voglibose. The efficacy of linagliptin is established only in the case that linagliptin shows superiority to placebo and voglibose simultaneously. Therefore, adjustment for multiple hypotheses is not carried out.

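### As worded, the exclusion attached to the 12-week analysis removes every placebo patient who completes week 12 and switches, contradicting the primary placebo comparison it belongs to

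*Protocol article*

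**What the plan says.** All statements are in the Protocol article.

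- **Analysis for the primary endpoint, 12-week model.** The dose factor is the "j-th dose group (j = 0: placebo, 1: 5 mg, 2: 10 mg". The text then says "Comparisons conducted at 12 weeks are between linagliptin and placebo", and the next sentence reads "Patients who received placebo for 12 weeks and are then randomized to receive either linagliptin 5 mg or 10 mg are excluded" from this analysis.
- **Same section, 26-week model.** This is introduced only later. Its treatment factor is the "j-th treatment group (j = 1:5 mg, 2:10 mg, 3:voglibose", with no placebo level.
- **Study Stages, text to Figure 1.** "Patients randomized to Group A will receive a placebo for 12 weeks after which they will receive linagliptin for 40 weeks".
- **Study Randomization.** Six sequences are listed. The only two that begin with placebo continue to linagliptin 5 mg or 10 mg. "Therefore all patients ultimately take either linagliptin 5 mg or 10 mg, unless they withdraw or drop out the study".
- **Study Endpoints.** Linagliptin 10 mg against placebo at 12 weeks is the primary comparison.
- **Statistical analysis.** Efficacy is analysed by intention to treat, in the full analysis set (FAS).
- **Discussion.** The 16-week HbA1c "levels in the placebo group will not be included in any comparison"; it is to be read as an indication of the population's untreated baseline.

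**The concern.** The exclusion names patients, not measurements, and it follows directly on the sentence about the 12-week comparison. The natural referent is therefore the 12-week model. The patients it describes are the control arm of that model: Group A patients who finish the placebo period and take up linagliptin as planned.

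Read literally, completers leave the placebo arm while linagliptin completers stay. The remaining controls would be people who left early, a selected group that may have no week-12 value. The defining event, a planned switch after the endpoint is measured, gives no reason to discard the week-12 result.

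The 12-week result also matters for conduct. The same section makes continuation of the study, and a dose change within it, depend on how linagliptin compares with placebo at 12 weeks. An ambiguous analysis set for that contrast carries into those decisions.

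**Working it through.** **1. Who is excluded.** Group A takes placebo for 12 weeks, then linagliptin for 40 weeks. Both placebo sequences end in linagliptin 5 mg or 10 mg, and no arm stays on placebo. So the excluded patients are all Group A patients who complete week 12 and switch. Only those who leave before the switch escape the rule.

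**2. Which measurement the Discussion bars.** Placebo washout is 4 weeks and randomized placebo is 12 weeks: 4 + 12 = 16 weeks. The Discussion itself gives 16 weeks as the longest placebo exposure. It refers to data after 16 weeks on placebo, so it cannot mean 16 weeks after randomization, when Group A is already on linagliptin. The barred value is the placebo arm's week-12 value.

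**3. The plan's own sample size reproduces.** Inputs from Sample size: difference 0.5, SD 0.9, one-sided 2.5%, power 90%, placebo to linagliptin 1:2.

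- n(placebo) = (1 + 1/2) × (1.960 + 1.282)² × 0.9² / 0.5² = 1.5 × 10.51 × 3.24 ≈ 51.1, rounded up to 52; linagliptin 104. This matches the stated figures.
- Power at 52 and 104: 0.5 / [0.9 × √(1/52 + 1/104)] = 3.27, giving 90.5% (normal) or 90.2% (noncentral t).

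The calculation is sound, and it needs at least 52 placebo patients with a week-12 value.

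**4. What the literal rule leaves (illustration only).** Placebo completers: 0. The plan expects 15% dropout over 52 weeks but does not say when it occurs, so a range is needed. Of 63 placebo patients, 0.15 × 63 = 9.45 leave in total.

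- All dropout before week 12 (assumption, upper limit): about 9 early leavers.
- Dropout spread evenly over 52 weeks (assumption): 9.45 × 12/52 = 2.18, about 2.

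Nominal power by noncentral t, difference 0.5, SD 0.9, one-sided 2.5%, against 126 linagliptin patients:

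| Placebo n | Noncentrality | Degrees of freedom | Power |
|---|---|---|---|
| 9 | 0.5 / [0.9 × √(1/9 + 1/126)] = 1.61 | 133 | 35.9% |
| 2 | 0.5 / [0.9 × √(1/2 + 1/126)] = 0.78 | 126 | 11.8% |

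Using 104 linagliptin patients instead changes little (35.4% and 11.7%). Both cases give every early leaver a usable week-12 value, which is generous, and neither accounts for selection.

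**The case against.** The strongest reply is that the intent is plain. The 12-week model has a placebo level, the primary comparison is against placebo, and the sample size counts placebo patients. An analyst applying the exclusion literally would have almost no placebo group to fit and would notice. This stands. A reader might infer that the primary analysis will be run without controls, or that the trial's power is really 12% to 36%. The document does not support either inference; those figures describe a literal application of one sentence, not the planned design.

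A second reply is that the sentence may belong where it is. The 12-week analysis is introduced in terms of 12 weeks of linagliptin treatment, and Group A patients also reach 12 weeks of linagliptin after their switch. The sentence may be meant to keep those later data out of the 5 mg and 10 mg groups. Equally, it may be meant for the 26-week analysis, which has no placebo level. Both are plausible and the text states neither, so it would be wrong to assert one of them as the intended meaning.

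On the 16-week value, it is fair to say that this is Discussion text, that it speaks of levels where the endpoint is change from baseline, and that the same section relies on the primary comparison being made. It is therefore the weaker part of the point. But the change is computed from the level, and a bar on any comparison is too broad as worded.

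That an article condenses the full protocol does not answer the point. This is no omitted detail: a rule on the primary analysis set is stated, and it conflicts with the sections around it.

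**Conclusion.** The point holds as a contradiction in the stated rule for the primary analysis set. As written, the exclusion takes out all placebo completers who switch. It cannot stand together with the placebo level of its own model, the primary comparison, the intention-to-treat/FAS basis, or the 52 placebo patients that the 90% power requires. The Discussion's bar on the 16-week value compounds it, because that value is the week-12 placebo value.

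The main harm, if the sentence were followed, is the loss of a valid control group. The figure of 0 completers follows from the text alone. The 2 to 9 early leavers and the 12% to 36% nominal power rest on assumed dropout timing and are not a measured loss. The sample size calculation itself is correct. Because the sentence concerns the control group of the primary comparison, it should be corrected even though the intended control group can be recognised from the rest of the article.

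**What to change.** Replace the exclusion sentence with two statements:

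1. All Group A patients in the FAS contribute their pre-switch week-12 HbA1c to the 12-week model, as the placebo level.
2. Group A data collected after the switch to linagliptin do not enter the 5 mg or 10 mg groups of either the 12-week or the 26-week model.

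Together these cover both plausible intentions. In the Discussion, replace the bar on any comparison with a statement that the placebo arm's value after 16 weeks on placebo (study week 12) is additionally described as a treatment-free reference.

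While rewording, drop the phrase suggesting that Group A is randomized after week 12, or reconcile it: Study Randomization says randomization happens once, at enrollment, whereas the text to Figure 1 speaks of a further randomization at the switch.

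The cost is a few sentences. No new data, visits or patients are needed, and the sample size is unchanged. If the full protocol or analysis plan carries the same exclusion sentence, it should be corrected there too.

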### Study Stages

This study includes three different stages, each with specific objectives, and will utilize four treatment arms (A-D) (see Figure 1). The objective of Stage 1 is to compare changes in HbA_1c _levels in patients receiving linagliptin with those receiving placebo at 12 weeks. The objective of Stage 2 is to compare changes in HbA_1c _levels in patients receiving linagliptin with those receiving voglibose after 26 weeks of treatment. The objective of Stage 3 is to determine the long-term safety and tolerability of linagliptin.

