### Study Endpoints

The proposed comparison of efficacy between linagliptin (5 and 10 mg) and both placebo and voglibose is based on changes in HbA_1c _levels from baseline at 12 and 26 weeks, respectively. The primary comparison between linagliptin 10 mg and placebo is planned at 12 weeks, and the comparison between linagliptin 10 mg and voglibose 0.6 mg is planned at 26 weeks. To investigate dose-response relationships, a subsequent comparison is made at those time points between linagliptin 5 mg and placebo (12 weeks) and voglibose 0.6 mg (26 weeks).

Other parameters of interest measured will include inhibition of plasma DPP-4 activity, the proinsulin/insulin ratio, the homeostasis model assessment (HOMA) indices for insulin resistance and insulin secretion, body weight, waist circumference and plasma concentrations of linagliptin. Adverse event, safety, laboratory and hematology data will be collected during the study and will form part of the secondary endpoint data for determining the long-term safety profile of linagliptin.

Patient reported outcomes will be assessed using the Diabetes Treatment Satisfaction Questionnaire (DTSQ) modified by Ishii [12], consisting of 6 items assessing treatment satisfaction and 2 items assessing the perceived frequencies of hyperglycaemia and hypoglycaemia.

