### Sample size

Sample size calculations are performed using nQuery Advisor^® ^6.0 (Statistical Solutions Ltd, Ireland) software on a Windows-based personal computer. On the basis of clinical studies conducted in Japan and other countries, it is estimated that the overall mean change in HbA_1c _levels after treatment with linagliptin 5 mg QD for 12 weeks will be approximately 0.5% compared with 0% in placebo. This will provide an overall mean between-groups treatment difference of 0.5%. Experience also suggests that the standard deviation of this difference will be approximately 0.9%. Employing an accepted one-sided statistical significance threshold of 2.5% and taking into account the weighting for placebo and linagliptin group randomization ratios (1:2), it is possible to predict a 90% power for the study with sample sizes of no less than 52 patients in the placebo group and no less than 104 patients in the linagliptin groups.

Assuming that HbA_1c _levels for the linagliptin treatment groups will continue to fall with ongoing therapy, estimates suggest that the mean change in HbA_1c _levels from baseline after a 26 week treatment with linagliptin 5 mg, will be approximately 0.7%, compared with 0.25% for voglibose 0.6 mg. It is expected that this difference between treatments will be reflected in a mean difference in HbA_1c _levels from baseline of 0.45% [16]. With a standard deviation of the difference at 1.0% and the level of significance set at 2.5% (one-sided analysis), sample sizes of 105 or more in each group provide a power greater than 90%.

Experience derived from previous clinical trials in patients with T2DM suggests that a discontinuation/dropout rate of approximately 15% can be expected during the current 52-week trial. Assuming that the present study will experience a similar level of subject discontinuation, it is possible to adjust the recruitment targets to maintain study power in anticipation of similar attrition levels. A target sample size of 63 patients in the placebo group and 126 patients each in the linagliptin and voglibose treatment groups (a total of 441 patients overall) is therefore required to power this study appropriately to achieve its primary objectives.

The sample size in the linagliptin group also appears to satisfy the requirements for evaluation of safety in the clinical development of new drugs expected for long-term use in non-fatal diseases [17].

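### The condition for the 26-week voglibose comparison is reversed: it is tied to failure against placebo, while the efficacy criterion requires superiority to both

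*Protocol article*

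**What the plan says.** All references are to the protocol article.

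- **Analysis for the primary endpoint** (condition): HbA1c values after linagliptin "are to be compared with those for voglibose after 26 weeks if linagliptin treatment fails to achieve a statistically significant difference" from placebo. A parenthesis ties this to the "primary comparison dose at 12 weeks". Study Endpoints identifies that dose as 10 mg.
- **Same paragraph** (stopping rule): "the study stops if neither of the linagliptin arms shows statistically significant differences from placebo" at 12 weeks.
- **Discussion** (success criterion): "The efficacy of linagliptin is established only in the case that linagliptin shows superiority to placebo and voglibose simultaneously". The next sentence draws the conclusion on multiplicity: "Therefore, adjustment for multiple hypotheses is not carried out".
- **Study Endpoints** (no condition): "the comparison between linagliptin 10 mg and voglibose 0.6 mg is planned at 26 weeks". The 5 mg comparisons come afterwards, at the same time points.
- **Study Stages** (no condition): the Stage 2 objective is to compare HbA1c changes, "levels in patients receiving linagliptin with those receiving voglibose after 26 weeks of treatment".
- **Background**: the comparison with voglibose is listed among the primary objectives.
- **Sample size**: the voglibose comparison has its own power calculation, with no condition attached.

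**The concern.** The condition links the trial's two primary comparisons. As worded, it calls for the voglibose comparison when the primary dose has not beaten placebo and does not call for it when the dose has. The Discussion needs the opposite: a dose that has beaten placebo must go on to be tested against voglibose.

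What is at stake is whether the testing sequence can be read in one way before the data are seen. If the sentence is followed, the second primary comparison is prompted where it can no longer support the claim for that dose. If it is quietly set aside after results are known, the sponsor will have chosen the confirmatory sequence with those results in hand.

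**Working it through.** **1. The plan's own figures reproduce.** Inputs are from Sample size, at one-sided 2.5%.

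- Week 12, linagliptin against placebo: difference 0.5, SD 0.9, 52 placebo and 104 linagliptin. SE = 0.9 × √(1/52 + 1/104) = 0.1529. The ratio is 0.5/0.1529 = 3.271. Normal-approximation power is Φ(3.271 − 1.960) = Φ(1.311) = 90.5%; the noncentral t gives 90.2%. The article states 90%.
- Week 26, linagliptin against voglibose: difference 0.7 − 0.25 = 0.45, SD 1.0, 105 per group. SE = √(2/105) = 0.1380. The ratio is 0.45/0.1380 = 3.261. Power is Φ(1.301) = 90.3%; the noncentral t gives 90.1%. The article states more than 90%.

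The sample sizes are therefore sound on these inputs, and the defect lies in the rule alone.

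**2. The rule, outcome by outcome.** Take the strict reading: the condition concerns 10 mg, and the voglibose test follows only when the condition is met.

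| Week-12 result | Voglibose test called for? | Stopping rule | Efficacy criterion for 10 mg |
|---|---|---|---|
| 10 mg beats placebo (5 mg either way) | No | Does not apply | Still open, but its second test is not called for |
| 10 mg fails, 5 mg beats placebo | Yes | Does not apply | Already lost |
| Both doses fail | Yes | Study stops before week 26 | Already lost |

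For 10 mg, being tested against voglibose requires failure against placebo, and success requires superiority to placebo. The two cannot occur together, so on this reading the probability that 10 mg meets the criterion is 0. This follows from logic and not from any effect size. The last row is the only one in which the condition and the stopping rule collide.

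**3. How often each row arises.** This was simulated (400,000 trials; normal test statistics with known SD; 52 placebo and 105 in each active arm). Two assumptions are not in the article. Both doses are given the planned effects, although Sample size states those effects for 5 mg. The within-patient correlation of the 12- and 26-week changes is set to 0, 0.5 and 0.8.

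- 10 mg beats placebo: about 91% (noncentral t at 52/104: 90.2%).
- 10 mg fails: about 9%, made up of about 5% in which 5 mg beats placebo and about 4% in which both fail.
- 10 mg fails and 5 mg beats both comparators: about 5%.

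**4. With the condition turned round, or removed.** The probability that 10 mg beats both placebo and voglibose is 82.0%, 82.5% and 83.0% for correlations 0, 0.5 and 0.8. At correlation 0 this is close to the product of the two powers in step 1: 0.905 × 0.903 = 0.817. The probability is the same whether the voglibose test follows success against placebo or is unconditional, because both tests must succeed in either case.

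**The case against.** The strongest reply is that this is one faulty sentence in a condensed article and that the rest of the text makes the intention plain. The sentence says if, not only if, and several sections plan the voglibose comparison without any condition. That stands. The document contradicts itself; it does not consistently bar the comparison. It does not excuse the sentence, which is complete, sits in the analysis section and is corrected nowhere else in the article.

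Three stronger readings are tempting and are not supported.

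- **That the trial can never succeed.** A reader might infer a zero chance overall. The zero applies to the gated dose on the strict reading. If 5 mg may be tested after 10 mg fails, 5 mg could still beat both comparators, in about 5% of trials under the assumptions above. Study Endpoints makes the 5 mg comparison subsequent to that of 10 mg, and the article does not say whether this path is open.
- **That the condition and the stopping rule always conflict.** They conflict only when both doses fail, or if linagliptin in the condition means both doses together. If 10 mg fails and 5 mg succeeds, both can be followed.
- **That the case for no multiplicity adjustment depends on the condition.** It does not. Requiring superiority to both comparators is an intersection-union criterion. For a given dose, each test may be run at one-sided 2.5%, in any order and with no gate, without inflating the error of the joint claim.

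It is also fair that the figure of about 90% borrows the 5 mg planning effect for 10 mg. It shows which branch is the likely one; the contradiction does not rest on it.

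**Conclusion.** The point holds as an error in a stated decision rule, most likely a drafting slip. The condition is reversed relative to the Discussion's efficacy criterion. It is inconsistent with Background, Study Stages, Study Endpoints and Sample size, and it collides with the stopping rule when both doses fail. Read strictly, the gated 10 mg dose has no route to the criterion. With the condition reversed or dropped, that route has a probability of about 82 to 83%. This range assumes the planned effects apply to 10 mg and a correlation of 0 to 0.8; the contradiction itself needs neither assumption. The position of 5 mg after a 10 mg failure is undetermined. The sample size stands, and so does the argument for making no adjustment between the two comparators for a given dose. The sentence must be corrected because it governs how the two primary comparisons are linked.

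**What to change.** Correct the sentence before unblinding, in one of two ways:

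- a dose's confirmatory week-26 comparison with voglibose is made if that dose was significantly superior to placebo at week 12; or
- the comparison is made unconditionally, as Study Endpoints has it, and efficacy is claimed for a dose only if both of its tests succeed.

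Either version fits the Discussion. The revised text should also say whether 5 mg can be tested confirmatorily after 10 mg has failed, and should be reconciled with the order in Study Endpoints (10 mg, then 5 mg) and with the closed testing procedure named in the analysis section. The condition and the stopping rule must be made consistent for the case in which both doses fail; how that case is handled clinically is for the sponsor to settle.

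The cost is one corrected sentence and a short clarification of the testing order. No patients, visits or data are affected.

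### The 26-week voglibose comparison is made conditional on linagliptin failing against placebo; the condition is the wrong way round and collides with the stop rule when both doses fail

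*Protocol article*

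**What the plan says.** Three sentences in the Protocol article, section Analysis for the primary endpoint, say what follows from the 12-week result:

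- **Voglibose sentence.** Linagliptin values "are to be compared with those for voglibose after 26 weeks if linagliptin treatment fails to achieve a statistically significant difference" from placebo. A parenthesis ties the condition to the primary comparison dose at 12 weeks.
- **Dose sentence.** "The dosing schedule for linagliptin increases from 5 mg to 10 mg during study if linagliptin 5 mg fails to demonstrate superiority to placebo". The test meant is the week-12 one, and nothing is said about the 10 mg result.
- **Stop sentence.** "the study stops if neither of the linagliptin arms shows statistically significant differences from placebo". This too refers to the week-12 result.

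Four other places bear on the same comparison:

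- Study Stages makes it the Stage 2 objective to compare HbA1c changes "in patients receiving linagliptin with those receiving voglibose after 26 weeks of treatment", with no condition attached.
- Study Endpoints fixes the week-12 test: "The primary comparison between linagliptin 10 mg and placebo is planned at 12 weeks". For week 26, again without any condition, it says that "the comparison between linagliptin 10 mg and voglibose 0.6 mg is planned at 26 weeks". For dose response, "a subsequent comparison is made at those time points between linagliptin 5 mg and placebo", and likewise against voglibose at 26 weeks.
- Sample size gives 105 patients per group for more than 90% power against voglibose.
- The Discussion states "The efficacy of linagliptin is established only in the case that linagliptin shows superiority to placebo and voglibose simultaneously", and uses this to justify making no multiplicity adjustment.

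**The concern.** The Discussion's criterion needs two wins. If a dose has beaten placebo, the voglibose result decides whether the claim is met. If a dose has not beaten placebo, no voglibose result can establish its efficacy. The voglibose sentence attaches the comparison to the second situation.

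The sentence also does not fit with the two that follow it. If neither dose beats placebo, it looks ahead to a 26-week comparison, the dose sentence moves 5 mg patients to 10 mg, and the stop sentence ends the trial. These cannot all be carried out, and no order of precedence is given. At stake is a decision rule for one of the trial's two main comparisons, to be applied once 12-week results are known, when an unclear rule is most awkward to interpret.

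**Working it through.** **Step 1. Reproduce the plan's power figures.** All inputs are from Sample size; tests are one-sided at 2.5%.

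- Week 12: difference 0.5%, SD 0.9%, 104 linagliptin and 52 placebo. SE = 0.9 × √(1/104 + 1/52) = 0.1529. Power = Φ(0.5/0.1529 − 1.96) = Φ(1.31) = 90.5% (90.2% with the noncentral t). The plan states 90%.
- Week 26: difference 0.45%, SD 1.0%, 105 per group. SE = 1.0 × √(2/105) = 0.138. Power = Φ(0.45/0.138 − 1.96) = Φ(1.30) = 90.3% (90.1% with the noncentral t). The plan states more than 90%.

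The sample-size figures are sound. The problem lies in the rule.

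**Step 2. Apply the three sentences to each 12-week outcome.** The article gives a planning effect for 5 mg only, so I assume first that 10 mg has the same 0.5%.

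- P(10 mg fails) = 1 − 0.905 = 9.5%, and the same for 5 mg.
- The doses share the placebo arm, so their test statistics have correlation (1/52)/(1/52 + 1/104) = 0.667. The bivariate normal then gives P(both fail) = 4.1%.
- P(only one named dose fails) = 9.5 − 4.1 = 5.4%.
- P(both succeed) = 100 − 4.1 − 2 × 5.4 = 85.1%.

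| Doses beating placebo at week 12 | Probability | Voglibose sentence | Dose sentence | Stop sentence | What the Discussion's criterion needs |
|---|---|---|---|---|---|
| Both | 85.1% | not triggered | not triggered | no | the voglibose test, for either dose |
| 10 mg only | 5.4% | not triggered | 5 mg raised | no | the voglibose test, for 10 mg |
| 5 mg only | 5.4% | triggered | not triggered | no | 10 mg can no longer qualify; 5 mg still could |
| Neither | 4.1% | triggered | 5 mg raised | stop | neither dose can qualify |

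In the first two rows the voglibose result is decisive for 10 mg, and the sentence is silent. In the last two rows it cannot help 10 mg, and the sentence applies. In the last row all three sentences are triggered and cannot all be followed.

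**Step 3. Vary the assumed effects.** Apart from the planning case, these are assumptions rather than figures from the article.

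| True 12-week effects | 10 mg fails | Both fail |
|---|---|---|
| both 0.5% | 9.5% | 4.1% |
| 10 mg 0.6%, 5 mg 0.5% | 2.5% | 1.5% |
| both 0.4% | – | 14.9% |
| both 0.3% | – | 36.5% |
| both 0 | 97.5% | about 96% |

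The last column shows how often the sentences conflict. It does not measure harm: with two ineffective doses, stopping is the right outcome.

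**The case against.** **The wording says 'if', not 'only if'.** A reader might infer that the voglibose comparison is skipped whenever 10 mg succeeds. On that reading it would not run for 10 mg in about 90% of trials under the planning assumptions, and 10 mg could never win both comparisons. With the condition corrected, the chance of winning both is about 0.905 × 0.903 = 82%, treating the two tests as independent. The documents do not support this contrast as a real loss: Study Stages and Study Endpoints plan the comparison without condition and Sample size powers it, so skipping it after success is plainly not intended. What remains is that the stated condition is attached to the wrong outcome.

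**Failure of 10 mg does not lose the whole trial.** A reader might also infer that the sentence is triggered only when the Discussion's criterion is out of reach. That is true for 10 mg but not in general, because the criterion speaks of linagliptin and names no dose. In 5.4 of the 9.5 percentage points in which 10 mg fails, 5 mg has beaten placebo.

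**The sentence may be a continuation rule.** It could mean that the trial goes on to week 26 even if the primary dose misses. That fits Study Stages and Study Endpoints, but the text does not say it, and a voglibose result still could not establish efficacy for a dose that missed against placebo. Since more than one repair is possible, the plan has to state which rule applies.

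**The stop sentence naturally overrides.** This is fair: it covers the narrower case, and a stopped trial has no week 26. It settles the double-failure case in practice, but the text does not say so, and it leaves the reversed condition untouched.

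**Conclusion.** The point holds: the condition is wrong as written. It contradicts the unconditional comparison in Study Stages and Study Endpoints, sits badly with the power given in Sample size, and runs against the two-win criterion in the Discussion. This part rests on the text alone.

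The direct conflict with the stop sentence is confined to the case where both doses fail: about 4% of trials at the planning effect, if 10 mg matches the 5 mg assumption; 1.5% if 10 mg has 0.6% and 5 mg has 0.5%; and about 96% if neither dose works. These figures assume normal test statistics and the evaluable numbers in Sample size.

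The likely explanation is a wording error. It does not show that the sponsor would omit the voglibose comparison after success. It should still be corrected, because it is a stated decision rule for a main comparison.

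**What to change.** Reword the three sentences to say that:

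1. A dose is tested against voglibose at 26 weeks, for the efficacy claim in the Discussion, if that dose achieved superiority to placebo at 12 weeks. The 10 mg dose comes first and 5 mg is the subsequent comparison, as in Study Endpoints.
2. The stop rule takes precedence when neither dose beats placebo.
3. The 5 mg dose is raised to 10 mg only if 10 mg beat placebo and 5 mg did not. Patients are analysed in their randomized group, in line with the intention-to-treat basis under Statistical analysis.

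Whether 5 mg keeps a confirmatory voglibose test when only 10 mg fails is a separate choice, which the documents do not settle here. It can be left to the closed testing procedure that the plan already names.

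The cost is editorial. No sample size, visit or treatment arm changes. The condition takes no power from the 10 mg claim, because the Discussion already requires both wins.
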